## Abstract

**Abstract:**

**Introduction:**

Sub-Saharan Africa (SSA), including Tanzania, is double-burdened with high rates of teenage pregnancy and new HIV infections among adolescent girls and young women (AGYW) aged 15–24 years. Moreover, pregnant AGYW living with HIV in SSA have poorer adherence and retention on HIV treatment and elevated risks of vertical HIV transmission to their infants, as compared with older women. This paper describes the methods for the ENGAGE project, aiming to investigate and optimise healthcare for prevention of vertical HIV transmission (commonly prevention of mother-to-child transmission (PMTCT)) for AGYW living with HIV in Tanzania.

**Methods and analysis:**

ENGAGE uses a mixed-methods design to co-create and prototype an intervention package for pregnant/postpartum AGYW living with HIV through three phases in three Tanzanian regions. Phase 1 characterises the problem by investigating care engagement and outcomes in a cohort of N=10 147 AGYW receiving PMTCT services in routine healthcare. Phase 2 uses qualitative interviews to understand the social-structural drivers of care engagement from the perspective of AGYW, healthcare providers and community stakeholders and an evidence review of potential solutions. In phase 3, we will use findings from phase 1 and 2 to co-create (together with AGYW and healthcare providers) an intervention package to optimise PMTCT care for most at-risk AGYW. The co-creation will be done through an intervention development action cycle, where ideas are presented, feedback sought and refinements made iteratively via several workshops over about 6 months. The resulting co-created intervention package will be prototyped at selected facilities/communities and refined into a final version, ready for piloting for feasibility, acceptability and preliminary effect in a later phase. This protocol focuses on the co-creation phase 3 and its preceding phases 1 and 2.

**Ethics and dissemination:**

ENGAGE has received ethical approval from the Tanzania National Health Research Ethics Committee (NIMR/HQ/R.8a/Vol.IX/4637), and the Swedish Ethical Review Authority (2024-05745-01) for analysis of data in Sweden. Findings will be disseminated to AGYW, healthcare providers, community stakeholders, health officials, researchers, policy makers and the wider local and global scientific community.

STRENGTHS AND LIMITATIONS OF THIS STUDYENGAGE employs sequential explanatory mixed methods to comprehensively understand and optimise prevention of mother-to-child transmission care engagement, retention and health outcomes for pregnant/breastfeeding adolescent girls and young women (AGYW) with HIV by first quantifying the problem, then exploring underlying reasons qualitatively, and thereafter co-create solutions with the AGYW and healthcare providers.A key strength is the participatory co-creation of interventions with the targeted beneficiaries (AGYW and stakeholders) ensuring their practical relevance and cultural appropriateness.The project benefits from analysing a large national cohort dataset; however, the findings may be influenced by variations in data quality and completeness, common in routine healthcare settings.Although the project aims to generate directly actionable evidence for policymakers, the focus on a single national context means the generalisability of the optimised care package to other contexts within sub-Saharan Africa may be limited.

## Introduction

 Four decades into the HIV pandemic, sub-Saharan Africa (SSA) remains the most affected region, home to 65% of the world’s almost 40 million people living with HIV and close to half of the 1.3 million new HIV infections.^1^ In SSA, two-thirds of annual new HIV infections occur among women of reproductive age, of whom adolescent girls and young women (AGYW) 15–24 years have more than three times higher risk of HIV infection than men of the same age.^2^ SSA also has the world’s highest rates of both teenage and unintended pregnancies and low rates of contraceptive use particularly among AGYW.^3^,^5^ Pregnant women with HIV who are not on anti-retroviral therapy (ART) jeopardise their survival and well-being and pose higher risk of vertical HIV transmission to their infants.^1^

Globally, among children 0–14 years old, 82% of the 120 000 new HIV infections yearly occur in SSA, with a majority (>90%) driven by vertical HIV transmission during pregnancy, childbirth or breastfeeding.^2^ Without any intervention, the risk of vertical HIV transmission can be as high as 45%.^6^ Effective use of ART among pregnant and breastfeeding women with HIV can reduce this risk to <2%.^7^ Starting all pregnant women with HIV on lifelong ART for their own HIV treatment and for prevention of vertical HIV transmission (commonly referred to as prevention of mother-to-child transmission, PMTCT) has thus been a game changer towards ending HIV infections in children.^8^ From 2010 to 2023, vertical HIV transmission declined by more than half globally due to better ART coverage,^1^ yet gaps remain, with five out of every six new HIV infections in children occurring in SSA.

Tanzania is among the twelve priority countries in the global alliance to end AIDS in children.^2^ The country has made significant progress in reducing vertical HIV transmission from 20% in 2010 to 8% in 2023, largely due to the improved ART coverage among pregnant women with HIV (98% in 2023).^2^ Nonetheless, the vertical HIV transmission rate in Tanzania is still higher than the global target of <5%.^2^

Evidence from studies in Tanzania and across SSA indicate that pregnant AGYW with HIV are lagging behind in PMTCT efforts^79^,^12^ and that their needs are not sufficiently addressed by existing standard of care.^13^ Longitudinal studies of women in PMTCT care in Tanzania found that AGYW had higher risks of poor PMTCT outcomes than older women, including twice the risk of high viral loads (>400 copies/mL) and 63% higher risk of attrition from HIV care.^7 10 12^ Similar findings have also been reported in other SSA countries.^11^ Rates of vertical HIV transmission among infants born to AGYW mothers with HIV in SSA are scarcely reported and appear to be up to three times higher than among infants of older women.^11 14^ A previous study in Tanzania observed a vertical HIV transmission rate at 18 months postpartum of 2.2% among adolescent mothers (aged <20 years) vs 1.4% among all mothers studied.^7^

Multiple risk factors affect uptake and retention in PMTCT services such as timing of ART initiation, HIV status disclosure, HIV stigma and fear of ART side effects.^13^ Social and gender norms, stigma and its socioeconomic consequences, limited resources and harmful laws disproportionately affect AGYW in the HIV epidemic, hindering their access to essential sexual and reproductive health and rights (SRHR) information and services.^14 15^

While quality evidence on AGYW is missing as previous studies mainly used age as a predictor, available data shows that the specific needs of girls and young women are not sufficiently addressed by standard PMTCT care.^11 13^ Promising strategies to improve uptake of PMTCT include youth-friendly services that emphasise confidentiality and address stigma associated with both teenage pregnancy and HIV and providing innovative models of social support, such as ‘peer mothers’ (also with HIV) accompanying women through PMTCT. However, these initiatives were typically designed *for* young women rather than in collaboration with them. Therefore, it is imperative to refine and effectively implement interventions to align with the specific needs and contextual nuances experienced by pregnant and postpartum AGYW living with HIV, including addressing unintended pregnancy, access to contraceptive services and SRHR in general.

Co-creation is a practical approach to stakeholders, such as girls and young women, healthcare providers (HCPs), community gatekeepers and researchers working together as equal partners to improve healthcare services. Co-creation has been defined as ‘a distributed and collaborative pattern of creative problem-solving that proactively mobilises public and private resources to jointly define problems and design and implement solutions’.^16^ Challenges remain in terms of how to involve most at-risk or vulnerable populations—such as AGYW living with HIV—effectively and equitably when co-creating healthcare interventions.

The ENGAGE aims to investigate and optimise PMTCT care and outcomes for pregnant and postpartum AGYW living with HIV in Tanzania. This protocol briefly describes procedures for the initial phases of the project, which aim to quantitatively assess patterns and trends of PMTCT service uptake, retention and health outcomes via analysis of routine health data (phase 1); to understand the context, drivers and potential solutions via qualitative interviews and systematic reviews (phase 2). These two preceding phases set the stage for phase 3 of ENGAGE, the main focus of this protocol, which aims to co-create and prototype a tailored package of intervention(s) to optimise PMTCT care for AGYW. A subsequent phase, which is beyond the scope of this protocol, will focus on pilot-testing the intervention package for feasibility and preliminary effect through a cluster-randomised trial.

## Methods and analysis

ENGAGE is a mixed-methods research embedded in routine healthcare. It uses a sequential explanatory design that begins with an analysis of quantitative cohort data on AGYW enrolled in PMTCT care, followed by a stepwise qualitative inquiry to co-create, prototype and later pilot-test a package of interventions that can be easily integrated to optimise existing care approaches. Drawing on the Hawkins *et al* model for co-creating and prototyping public health interventions,^16^ the project is organised into four phases as shown in figure 1.

**Figure 1 F1:**
[figure not shown]
Conceptual framework, adapted from Hawkins *et al*.^16^ PMTCT, prevention of mother-to-child transmission.

Phase 1 will focus on characterising the problem through a cohort study, using a large registry-based routine healthcare database on AGYW enrolled in PMTCT care in Tanzania. Phase 2 will involve qualitative consultations to understand the context and drivers of care engagement for pregnant and postpartum AGYW living with HIV and an evidence review of potential solutions available in literature. Building on findings from these activities. Phase 3 will focus on co-producing and prototyping an intervention package to optimise PMTCT care together with pregnant/postpartum AGYW living with HIV and other key stakeholders. The intervention package will later be piloted for feasibility, acceptability and effect size estimation using a randomised controlled design (in a subsequent Phase 4). This protocol focuses on phase 3 and its preceding phases 1 and 2; details on phase 4 will be published in a subsequent protocol. Preparatory activities for the study commenced in April 2023, with activities for phases 1 and 2 rolled out between 2024 and 2025, and phase 3 during November 2025–2026.

### Patient and public involvement

ENGAGE is designed to incorporate patient and public involvement during the implementation of phase 3, which entails co-designing an interventions package to optimise PMTCT care for pregnant and postpartum AGYW living with HIV. This phase involves actively working with the AGYW, young peer mothers (also living with HIV) and HCPs as designers of the interventions whereas their spouses/partners, parents and other community members are involved as the sounding board, to review and provide feedback on the co-designed interventions.

### Study setting and population

ENGAGE will be conducted in three Tanzanian regions representing both urban and rural settings: Dar es Salaam, Kagera and Tabora. Dar es Salaam is predominantly urban, the most populous and the commercial hub of Tanzania, with 5.4 million of the country’s 62 million population. In contrast, Kagera and Tabora are predominantly rural, with populations of 3.0 million in Kagera and 3.4 million in Tabora.^17^ The adult (aged ≥15 years) HIV prevalence is 4.2% in Dar es Salaam, 5.7% in Kagera and 5.6% in Tabora.^18^ Each of the three regions registers about 140 000–200 000 new pregnant women in ANC annually, of which 20%–27% are AGYW and 3%–4% are living with HIV.^19^ The study population includes pregnant/postpartum AGYW living with HIV (new, previously diagnosed and transfers) and their infants. Specific details of the target population for each phase and research activity are described below.

In Tanzania, the PMTCT care cascade starts with HIV testing of all pregnant women at ANC. Those diagnosed with HIV are initiated on a lifelong ART regimen, and their HIV viral load and CD4 count are monitored. The cascade continues after delivery with emphasis on maternal ART adherence and retention, infant ARV prophylaxis, early infant HIV diagnosis (EID), counselling on breastfeeding/infant feeding, postpartum contraceptives and psychosocial support. Women already on lifelong ART follow the same procedures.^20^ HIV care in Tanzania, including PMTCT services, is provided by the Government free of charge in public health facilities and at a subsidised cost (including free ARVs) in private facilities. The services are supported by the United States President’s Emergency Plan for AIDS Relief (PEPFAR) and the Global Fund through implementing partner organisations. At the three study regions, Management and Development for Health (MDH) is the main implementing partner supporting HIV and PMTCT services, funded by PEPFAR via the US Centers for Disease Control and Prevention. Individuals diagnosed with HIV in Tanzania are assigned a unique identification (ID) number at enrolment in HIV care and treatment clinic (CTC-ID), which is used to register, record and manage their ART care data using facility-based charts (CTC2 cards). Data from CTC2 cards are entered into the national electronic CTC2 database. On transfer between ART clinics, this CTC-ID uniquely identifies, links and tracks care and records across facilities. On delivery, infants of women with HIV are issued unique HIV exposed infant IDs, linked to their mother’s CTC-ID, and are registered in HEI cards and CTC2 database, which are used to record and track their care, including EID tests.

### Partnerships

ENGAGE is a collaborative project implemented by MDH in Tanzania in partnership with the Department of Global Public Health at Karolinska Institutet (KI), Sweden. In Tanzania, the project also engages collaborators from the Ministry of Health (MoH), the President’s Office Regional Authorities and Local Government (PORALG), Muhimbili University of Health and Allied Sciences (MUHAS) and the Regional Health Management Teams from the three study regions.

### Phase I: characterising the problem (aims 1–3)

This cohort study will use data from routine healthcare records from 559 health facilities supported by MDH, which account for over 90% of the HIV care in the three regions. Participants will comprise all pregnant/postpartum AGYW living with HIV who started PMTCT services between 1 January 2018 and 31 December 2020 and their infants born from this pregnancy/breastfeeding episode, referred to herein as the index pregnancy. Study participants will be followed for at least 2 years postpartum (until 31 December 2023) to allow enough time for final vertical HIV transmission status to be ascertained and documented (ie, 24+ months post partum). The data source will be CTC2 database, which stores data on HIV care and PMTCT services in Tanzania. Primary outcomes include: (1) time to ART attrition, defined as discontinuing ART for any reason, including death, stopping ART or loss to follow-up for >90 consecutive days from scheduled appointment; (2) detectable viral load defined as ≥50 viral copies/mL of blood after at least 3 months of ART use for those who started ART at enrolment while those already on ART detectable VL after enrolment and (3) HIV-free infant survival defined as infants who are alive and tested negative at final HIV test by 18+ months postpartum or by the last available data point. We will also evaluate repeat pregnancy, which is defined as any subsequent pregnancy occurring after the index pregnancy up to 2 years post partum. Statistical analysis will be performed using STATA software version 18, employing the Kaplan-Meier method and Cox regression models to assess time to ART attrition, HIV-free infant survival, repeat pregnancy and generalised linear models for detectable viral load. Statistical significance will be determined using a p value threshold of <0.05.

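### Primary outcome 3 accepts a last-observation status as HIV-free infant survival, which does not fit the planned Kaplan-Meier/Cox analysis and can carry untested, exposed time as event-free

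*Protocol article*

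**What the plan says.** The section on Phase I (characterising the problem) lists HIV-free infant survival as the third primary outcome. It counts infants "alive and tested negative at final HIV test by 18+ months postpartum or by the last available data point". No minimum age is set for the final test when the second branch applies, and the test need not follow the end of breastfeeding.

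On analysis, the section plans "employing the Kaplan-Meier method and Cox regression models to assess time to ART attrition, HIV-free infant survival, repeat pregnancy". For this outcome it gives no event date and no censoring date.

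On follow-up, the cohort is women "who started PMTCT services between 1 January 2018 and 31 December 2020". "Study participants will be followed for at least 2 years postpartum (until 31 December 2023"), and the reason given is "to allow enough time for final vertical HIV transmission status to be ascertained and documented (ie, 24+ months post partum").

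**The concern.** Two different quantities are joined by one 'or'. The first is a status at 18 months or later. The second is whatever was last recorded, which may be a single negative test soon after birth. The Introduction names breastfeeding as a route of transmission, so the later status of an infant in the second group is unknown, not HIV-free. Deaths after the last record are also unseen.

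The definition describes a good outcome reached, while the analysis needs a failure, its time, and a rule for when observation stops. The last available data point is also not necessarily the last negative test. An infant tested early and seen later without a test could be carried as event-free through exposed time in which infection was never looked for.

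Loss is plausibly related to risk. The Introduction reports that young women in Tanzanian programmes had 63% more attrition and double the risk of a high viral load compared with older women. Infant records are linked to the mother's clinic number (Study setting and population), so infant and maternal loss may well coincide. What is at stake is the level of a primary outcome in the phase meant to characterise the problem.

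**Working it through.** The article gives no event, power or sample-size calculation for this outcome, so there is no planned figure to reproduce. Two checks were made.

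**1. Does the calendar cut-off force the fallback?** Take the latest case: enrolment on 31 December 2020 at the very start of pregnancy. With an assumed 280-day pregnancy, delivery falls on 7 October 2021. From then to 31 December 2023 is 815 days, and 815 / 30.44 = 26.8 months. Every index birth can therefore reach 18 and 24 months before the cut-off. The fallback acts essentially on infants whose later records are missing.

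**2. What does the handling of those infants do to the estimate?** A two-period model:

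- R = true 18-month risk. Scenarios: 2.2% (Introduction, adolescent mothers, 18 months) and 8% (Introduction, national rate, 2023). Both are transmission figures without death and serve only to set a scale.
- e = share of events found by the early test, assumed 30–60%.
- L = share of early-negative infants lost straight after that test, assumed 10–40%.
- k = late risk of lost infants relative to retained infants, assumed 1–2.

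The documents give none of e, L or k. Write E = eR and D = (1 − L) + Lk. Then:

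- lost infants scored HIV-free: estimate = E + (R − E)(1 − L)/D
- lost infants censored at their last negative test: estimate = E + (R − E)/D

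Example with e = 0.3 and L = 0.25:

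| True R | k | Scored HIV-free | Censored at last negative test |
|---|---|---|---|
| 2.20% | 1 | 0.66 + 1.54 × 0.75 = 1.81% | 0.66 + 1.54 = 2.20% |
| 2.20% | 2 | 0.66 + 1.54 × 0.75/1.25 = 1.58% | 0.66 + 1.54/1.25 = 1.89% |
| 8.00% | 1 | 2.4 + 5.6 × 0.75 = 6.60% | 2.4 + 5.6 = 8.00% |
| 8.00% | 2 | 2.4 + 5.6 × 0.75/1.25 = 5.76% | 2.4 + 5.6/1.25 = 6.88% |

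Divided by R, both formulas depend only on e, L and k, so the relative error does not rest on the choice of 2.2% or 8%. The extremes are:

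- Scored HIV-free, smallest error (e = 0.6, L = 0.1, k = 1): 1 − (0.6 + 0.4 × 0.9) = 4%.
- Scored HIV-free, largest error (e = 0.3, L = 0.4, k = 2): 1 − (0.3 + 0.7 × 0.6/1.4) = 40%.
- Censored, k = 1: 0% throughout.
- Censored, k = 2, smallest (e = 0.6, L = 0.1): 1 − (0.6 + 0.4/1.1) = 4%.
- Censored, k = 2, largest (e = 0.3, L = 0.4): 1 − (0.3 + 0.7/1.4) = 20%.

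In absolute terms, scoring lost infants HIV-free gives 1.32–2.11% for a true 2.2% and 4.80–7.68% for a true 8%. Censoring with doubled late risk gives 1.76–2.12% and 6.40–7.71%.

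If infants are kept at risk beyond their last negative test, up to the 18-month horizon, they stay in the denominator with no chance of a recorded infection. The Kaplan-Meier estimate then equals the first formula. Naming Kaplan-Meier helps only if censoring is at the last negative test.

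**The case against.** The strongest reply is that the same section names Kaplan-Meier and Cox regression. Under those methods, an infant whose record ends with an early negative test is event-free to that point and then censored. The last available data point can be read as an end-of-observation clause, and the complement of alive and negative is death or a positive test, so the event is implied. Dating and censoring rules commonly sit in a full protocol or analysis plan, neither of which is shown, and the article says it describes Phases 1 and 2 only briefly.

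Much of this stands. A reader might infer that transmission will certainly be understated. The documents do not support that, because one ordinary reading of the plan already censors these infants. What the reply leaves open is the printed definition. The article writes ART attrition as a time to a named event with a 90-day loss rule, and defines repeat pregnancy as an event. Only this outcome is printed as a favourable status, and its end point need not be the last negative test.

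Three other stronger readings should be set aside:

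- A reader might treat 2.2% and 8% as risks after an early negative test and derive a much larger loss of failures. The first is total transmission at 18 months and the second a national rate. Neither is a late risk among lost infants.
- A reader might infer that infants of mothers already lost never enter the denominator, because "infants of women with HIV are issued unique HIV exposed infant IDs" on delivery. The article does not say that they are excluded, and it defines the cohort to include the women's infants.
- A reader might infer that the association between maternal attrition and infant infection will be weakened or reversed. The article does not state that this association will be estimated, and no calculation here shows a reversal.

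Nor is the 24-month rationale contradicted. It explains the length of follow-up, and the fallback merely does not require that status to be reached.

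**Conclusion.** The point holds as a defect in the definition of a primary outcome. It mixes a status at 18 months or later with a last-observation status and does not match the time-to-event analysis assigned to it. The direction of any resulting error is towards too few failures when lost infants are at the same or higher late risk.

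The size depends on a choice that the article leaves open. It is about 4–40% in relative terms if the status is used as a proportion or infants are carried event-free to the horizon. It is nil if infants are censored at the last negative test and loss is non-informative, and about 4–20% if they are so censored but lost infants have double the late risk. These ranges rest on the assumed loss, early share and risk ratio above. Unrecorded deaths among lost infants are not modelled and would add to the understatement.

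**What to change.** - Define the event as infant HIV infection or death, with time from birth.
- Censor event-free infants at their last negative test, not at last contact or the cut-off date.
- Delete the last-available-data-point branch, and reserve the label 'HIV-free at 18+ months' for infants with a negative test at that age.
- Report Kaplan-Meier HIV-free survival at 18 and 24 months, with the number of index births that have no infant record or no final test.
- Add one sensitivity analysis for informative loss, for example inverse-probability-of-censoring weights.

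The cost is one reworded definition and a little more analysis of data already extracted. The reported HIV-free survival will be somewhat less favourable and less precise.
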